## Abstract

**Background:**

Left atrial appendage closure (LAAC) procedures prevent cardioembolic stroke in patients with atrial fibrillation who have contraindications to oral anticoagulant medications. However, these procedures carry certain risks of peri-procedural complications. One such complication is silent brain infarcts (SBI), which can lead to cognitive impairment and mood disturbances. The implementation of mechanical neuroprotection systems during LAAC procedures may reduce the risk of SBI and associated cognitive and mood disorders.

**Methods:**

The LAAC-SBI trial is a prospective, multicenter, randomized, and double-blind interventional study. The study aims to enroll a total of 240 patients, with 120 patients allocated to each group. The study group will evaluate the use of the Sentinel CPS during LAAC, while the control group will undergo LAAC procedures without the Sentinel CPS. The primary endpoint of the study is the number of new SBIs or stroke foci detected by diffusion-weighted magnetic resonance imaging (DW MRI). Secondary endpoints include deterioration of cognitive function, development of dementia syndrome, and occurrence of depressive disorders. These endpoints will be assessed using questionnaire tools such as the Montreal Cognitive Assessment (MoCA), Trail Making Test (TMT), Controlled Oral Word Association Test (COWAT), and Hospital Anxiety and Depression Scale (HADS). The observational period for patients in the study is 2 years.

**Discussion:**

If the study demonstrates a favorable outcome with reduced incidence of SBI and improved cognitive and mood outcomes in patients receiving cerebral protection devices during LAAC, it will have significant implications for clinical management standards. This would support the use of neuroprotection devices not only for LAAC but also in procedures such as atrial fibrillation ablation or transcatheter mitral valve interventions, where the risk of embolic events and subsequent brain injury may also be present.

**Trial registration:**

ClinicalTrials.gov NCT05369195. Registration on 11.05.2022.

## Introduction

### Background and rationale {6a}

Atrial fibrillation (AF) is considered the most significant risk factor for stroke. A patient registry conducted across 47 countries revealed that approximately 4% of patients experienced a stroke within 1 year of being diagnosed with AF, and approximately 11% died [1]. Therefore, patients who obtain a score of ≥ 2 points on the CHA2DS2-VASc scale are classified as having Class I indications for stroke prophylaxis by the European Society of Cardiology (ESC). While oral anticoagulants remain the cornerstone of treatment, some patients may have contraindications to these medications. In such cases, transcatheter left atrial appendage closure (LAAC) serves as an alternative method for stroke prevention.

The effectiveness and safety of LAAC procedures have been established through extensive research involving randomized and observational trials [2–4]. Furthermore, it has been demonstrated that LAAC provides superior survival benefits compared to warfarin therapy [5]. However, it is important to acknowledge that the LAAC procedure carries certain risks, such as periprocedural stroke and microembolization of cerebral blood vessels, leading to SBI. The risk of periprocedural stroke is reported to be 0.17% [6]. Thus far, only limited data regarding the prevalence of LAAC-related SBI have been published. The incidence of SBI in these studies ranged from 4.8 to 52% [7–10]. Prospective and observational studies have provided evidence linking cognitive decline and the development of dementia to SBI [11]. A meta-analysis of 31 studies estimated the overall risk of dementia in AF patients with SBI at 1.48 [12].

#### Rationale

Evidence from randomized trials demonstrates that cerebral protection systems can effectively reduce the risk of complications such as stroke and SBI during transcatheter aortic valve implantation (TAVI). Devices like TriGuard, Sentinel Cerebral Protection System (CPS), and Embrella have been specifically developed for this purpose. The Sentinel CPS device has been evaluated in the randomized trials CLEAN-TAVI, MISTRAL-C, and Sentinel-H during TAVI procedures. The CLEAN-TAVI single-center study involved 100 patients randomly assigned in a 1:1 ratio to undergo TAVI procedures, either with or without neuroprotection. The study documented a statistically significant reduction in both the number and volume of new ischemic brain lesions observed on diffusion-weighted magnetic resonance imaging (DW-MRI) at 2 and 7 days post-intervention (39% and 51% reduction, respectively) in the protected regions and the entire brain (*p*-values ranging from < 0.001 to 0.02) among patients who received the Sentinel CPS compared to those receiving standard care without brain protection [13].

In the multicenter MISTRAL-C study, 65 patients were enrolled. Although there was a lower number of SBI foci and a reduced SBI volume (95 mm^3^ vs. 197 mm^3^) on DW-MRI in the group with the Sentinel CPS compared to the group without neuroprotection, the difference did not reach statistical significance. Furthermore, 27% of patients in the Sentinel CPS group had no new SBI occurrences, compared to only 13% in the control group. Additionally, multiple (> 10) SBI foci were only observed in the control group. Patients who used the Sentinel CPS device also exhibited less cognitive impairment on the Mini-Mental State Examination (4% vs. 27%; *p* = 0.017) [14].

The most extensive multicenter and prospective study, SENTINEL-H, involved 217 patients undergoing TAVI. Using the Sentinel CPS device was associated with minimal risk to patients, as indicated by the high success rate of device insertion and removal (94.4%) and only one case (0.4%) of access site vascular injury. Strokes occurred in 5.6% of patients treated with the Sentinel CPS, compared to 9.1% in the control group. Among patients who experienced a stroke, the size and number of DW-MRI lesions were reduced when the Sentinel CPS was employed. The study revealed a correlation between SBI volume and cognitive decline (*r* =  − 0.25; *p* = 0.002 for protected areas); however, the differences between the study and control groups were not statistically significant. The study’s authors attributed this finding to significantly reduced cognitive functions at the study’s baseline [15].

In the DEFLECT III study, which included 85 randomized patients, the TriGuard system was compared to no neuroprotection during TAVI. The use of the TriGuard system was associated with a higher rate of no new SBI occurrences (26.9% vs. 11.5%), a lower incidence of neurological deficits assessed by the National Institutes of Health Stroke Score (NIHSS) (3.1% vs. 15.4%), and better outcomes on the Montreal Cognitive Assessment (MoCA) test. Additionally, patients using the TriGuard system were twice as likely to experience cognitive function normalization in the MoCA test after 30 days (45.5% vs. 20%; RR 2.27 [95% CI 1.01, 5.1]) [16].

The Sentinel CPS has received approval to prevent embolism by capturing and removing embolic materials, such as clots or fragments, that may enter the cerebral vasculature during endovascular procedures. However, it should be noted that the embolic material encountered during TAVI procedures differs from the embolic material found in the left atrial appendage (LAA) in structure, quantity, and nature. No randomized trials have been conducted to specifically assess the impact of using neuroprotective devices during LAAC. Only isolated cases of utilizing such devices during LAAC procedures have been described. The largest reported sample includes six patients with a thrombus present in the LAA, in whom the implementation of brain protection devices prevented the occurrence of overt stroke. However, cognitive function assessments were not conducted before and after the procedure, and no brain imaging studies were performed [17].

### Objectives {7}

The objective of the present study was to investigate the occurrence of SBI and evaluate the impact on cognitive function and the prevalence of mood disorders in patients with AF who underwent LAAC utilizing the Amplatzer Amulet occluder, with or without the utilization of the Sentinel CPS. The study aimed to test the hypothesis that using the Sentinel CPS would mitigate the risk of SBI, cognitive decline, and depression in these patients.

### Trial design {8}

The LAAC-SBI trial is designed as a prospective, multicentre, randomized, and double-blind interventional study. Its primary objective is to recruit a total of 240 patients, with an equal allocation of 120 patients to each group. The study group will examine the effectiveness of utilizing the Sentinel CPS during LAAC procedures, whereas the control group will undergo LAAC without using the Sentinel CPS (Fig. 1). The study was designed to demonstrate the superiority of an experimental procedure, i.e. the use of Sentinel CPS during LAAC, over a control intervention.

**Fig. 1 Fig1:**
[figure not shown]
Flow diagram

## Methods: participants, interventions, and outcomes

### Study setting {9}

This study is being started by an academic hospital. The study intends to involve eight centers located in Poland. You may find a current and complete list of these collaborating hospitals on ClinicalTrials.gov.

### Eligibility criteria {10}

The study will enroll patients who meet the following criteria:Aged ≥ 18 yearsDiagnosed with paroxysmal, persistent, or permanent AFESC class I indications for preventing ischemic stroke, indicated by a CHA2DS2VASc score of ≥ 2Contraindications to anticoagulant use or a high bleeding risk based on a HAS-BLED score of at least 3 points

Patients meeting any of the following criteria will be excluded from the study:History of ischemic strokeHistory of central nervous system infectionsNeurological diseases such as Parkinson’s disease, Huntington’s disease, Creutzfeldt-Jakob disease, and Pick’s diseaseSevere mental disorders, including dementia of any etiology, schizophrenia, bipolar disorder, and depressionAnatomical obstacles to the LAAC procedure or the insertion of a neuroprotection systemPresence of mechanical heart prostheses

### Who will take informed consent? {26a}

Patients participating in the study must be familiar with the information presented in the informed consent form and give it in writing in the investigator's presence.

### Additional consent provisions for collection and use of participant data and biological specimens {26b}

The study does not provide for additional sample collection, which would require additional consent from study participants.

## Interventions

### Explanation for the choice of comparators {6b}

Patients enrolled in the study will undergo LAAC procedures conducted using the standard approach. However, only the study group will exclusively integrate the CPS Sentinel neuroprotection system during this procedure. The selection of this specific neuroprotection system stems from its approval for clinical use and its capability to safeguard approximately 95% of brain tissue from potential embolisms during intracardiac interventions.

Furthermore, the favorable outcomes observed when implementing the CPS Sentinel in patients undergoing TAVI procedures are compelling evidence of its high effectiveness. As a result, the researchers have chosen this system for investigation in the context of LAAC procedures to assess its potential benefits in reducing embolic events and enhancing patient outcomes.

### Intervention description {11a}

The LAAC procedure in the study group will involve the utilization of Amplatzer Amulet occluders along with the Sentinel CPS for cerebral circulation protection. Transcatheter LAAC interventions will be carried out under deep sedation or general anesthesia, using right femoral vein access.

The procedure encompasses several key steps to ensure accurate and safe placement of the Amplatzer Amulet occluder. Initially, a guide is positioned in the superior vena cava via the right femoral vein to establish a pathway for accessing the left atrium. Subsequently, a transeptal catheter is introduced and gradually withdrawn through the first and second slopes (foramen ovale) until access to the left atrium is achieved. This puncture process is meticulously monitored using fluoroscopy and transesophageal examination to ensure precise needle positioning and safety during atrial septum puncture.

Once left atrium access is established, a catheter is guided to the left atrial appendage (LAA) for angiography, providing a detailed assessment of LAA anatomy. Following this, the catheter is advanced to the left upper pulmonary vein and replaced with a specialized catheter designed for LAAC. The catheter is carefully positioned within the LAA at the appropriate depth, and a self-expanding Amplatzer Amulet occluder is inserted to close the LAA effectively. After successful occluder deployment, it is carefully pulled to verify proper positioning and assess the efficacy of LAA elimination. Finally, the guide catheter is removed, and a hemostatic suture is applied to the groin to ensure proper closure and minimize bleeding risk.

In the study group, before the LAAC procedure, a Sentinel CPS will be inserted to provide neuroprotection. Several steps are undertaken during the insertion of the Sentinel CPS. Firstly, arterial access is obtained through a radial artery puncture, and a pigtail catheter is inserted into the ascending aorta to perform aortography, assessing the aortic arch and cerebral arteries’ anatomy. The proximal filter of the Sentinel CPS is expanded in the brachiocephalic trunk, and the device is carefully rotated in the ascending aorta to position its tip in the left common carotid artery accurately. Subsequently, the distal filter of the Sentinel CPS is expanded, and fluoroscopy is used to ensure the correct positioning of both filters, thereby providing neuroprotection during the LAAC procedure.

After the successful implantation of the occluder in the LAA, the Sentinel CPS will be removed. The activated clotting time (ACT) must be maintained above 250 s during the procedure. Therefore, heparin will be administered. In the control group, heparin will be administered after the transeptal puncture. In the control group, the LAAC procedure will be performed in the same manner as in the study group but without installing the Sentinel CPS.

### Criteria for discontinuing or modifying allocated interventions {11b}

Analyses within the study will be carried out in accordance with the principle of intent-to-treat. Consequently, should a participant assigned to the study group not receive the Sentinel CPS intervention, they will still be retained within the study group. There will be no reassignment of participants between the study and control groups.

### Strategies to improve adherence to interventions {11c}

Given the interventional nature of this study, strategies for monitoring adherence pertain to the execution of follow-up visits and the associated procedures delineated for such instances. During follow-up visits, patients will be scheduled for subsequent appointments and receive timely telephonic reminders ahead of their impending appointments.

### Relevant concomitant care permitted or prohibited during the trial {11d}

Participation in the study does not influence the treatment of alternative medical conditions. Concerning prior therapeutic approaches, the patient enrolled in the study will not use oral anticoagulants after the procedure. Instead, they are advised to undergo dual antiplatelet therapy for 3 months post-LAAC intervention.

### Provisions for post-trial care {30}

The study incorporates an insurance policy designed to address any potential harm experienced by participants. After completing participation in the study, patients will no longer be obligated to undergo oral anticoagulant treatment as a component of stroke prevention in cases of atrial fibrillation. Instead, they will solely be recommended to take acetylsalicylic acid.

### Outcomes {12}

The study’s primary endpoint is the number of new SBIs or stroke foci in the DW MRI. In addition, the following secondary endpoints were defined:Volume of SBI and stroke foci in DW MRIDeterioration of cognitive functions assessment using standardized tests: The Montreal Cognitive Assessment (MoCA) test versions 8.1 and 8.3, Trail Making Test (TMT) parts A and B, Controlled Oral Word Association Test (COWAT)Development of dementia syndromeOccurrence of depressive disorders using Hospital Anxiety and Depression Scale (HADS)Presence of embolic material in the filters of the neuroprotection deviceComplications related to the use of the neuroprotection system during LAAC

### Participant timeline {13}

The participant timeline is shown in Table 1.

**Table 1 Tab1:** Schedule of enrolment, interventions, and assessments

	**STUDY PERIOD**							
	**Enrolment**	**Allocation**	**Post-allocation**					**Close-out**
**TIMEPOINT****	***Visit 0***	**Allocation**	***Visit 1***	***Intervention***	***Visit 2***	***Visit 3***	***Visit 4***	***Visit 5***
**ENROLMENT:**								
**Eligibility screen**	X							
**Informed consent**	X							
***Laboratory tests***	X							
***Transesophageal echocardiography***	X							
***Transthoracic echocardiography***	X							
***Carotid artery ultrasonography***	X							
***Electrocardiogram***	X							
***DW MRI***	X							
**Allocation**		X						
**INTERVENTIONS:**								
***LACC procedure***				X				
**ASSESSMENTS:**								
***DW MRI***					X			X
***Neurological assessment/NHSS***			X		X		X	X
***MoCA***			X		X	X	X	X
***TMT A&B***			X		X	X	X	X
***COWAT***			X		X		X	X
***HADS***			X				X	X
***EQ-5d-5L***			X				X	X
***Laboratory tests***			X		X	X	X	X
***Transesophageal echocardiography***			X			X	X	X
***Transthoracic echocardiography***			X				X	X
***Carotid artery ultrasonography***								X

### Sample size {14}

Based on the assumptions that cerebral protection during LAAC would result in a favorable response in 85% of patients and that the absence of new SBI on DW MRI in the control group would affect 70% of patients, the minimum group size was estimated to be 118 individuals per group. This estimation ensured 80% power to detect the anticipated difference at a significance level of 5%. Considering a withdrawal or invalidation ratio of 2%, a total of 120 individuals will be enrolled in each group, resulting in a sample size of 240 patients for the study. This sample size is necessary to provide sufficient statistical power and enable meaningful comparisons between the study and control groups.

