## Statistical methods

### Statistical methods for primary and secondary outcomes {20a}

The primary analysis of all endpoints will be conducted using an intention-to-treat approach, wherein participants will be analyzed according to their initial randomization assignment, irrespective of the actual treatment received. Quantitative variables will be presented as either mean or median values, while qualitative variables will be reported as counts (with percentages). To assess the distribution of quantitative variables, the skewness index will be employed. Between-group comparisons will be carried out using independent *t*-tests and ANCOVA for quantitative variables. A chi-square test will be used to compare distributions between the two groups for qualitative variables.

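### The primary endpoint is a lesion count, but the sample size and the 80% power are for a yes/no outcome, so power for the stated primary analysis is not established

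*Protocol article*

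**What the plan says.** Three sections bear on this.

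- **Endpoint.** Outcomes {12}: "The study’s primary endpoint is the number of new SBIs or stroke foci in the DW MRI". The Methods paragraph of the Abstract says the same. This is a per-patient count.
- **Analysis.** Statistical methods {20a} has one general rule by type of variable: "Between-group comparisons will be carried out using independent *t*-tests and ANCOVA for quantitative variables", and "A chi-square test will be used to compare distributions between the two groups for qualitative variables". It adds: "To assess the distribution of quantitative variables, the skewness index will be employed". No sentence assigns a test to the primary endpoint by name. A count is quantitative, so the general rule leads to a t-test or ANCOVA.
- **Sizing.** Sample size {14} assumes a favourable response in 85% of protected patients and, for controls, that "the absence of new SBI on DW MRI in the control group would affect 70% of patients". From this it derives 118 per group for 80% power at the 5% level, and 120 per group after a 2% allowance. It gives no mean, standard deviation or dispersion for the lesion count.

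Freedom from new SBI, the outcome used for sizing, is neither a primary nor a secondary endpoint in {12}.

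**The concern.** A power statement holds for one endpoint and one test. Here the endpoint is a count, the general analysis rule compares means, and the power was calculated for a difference in proportions. The two agree only in special cases, for example if every patient with a lesion had exactly one.

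The gap is wide because of the plan's own assumption: with 70% and 85% of patients lesion-free, most counts are zero. The mean then depends on the minority with lesions, and a few patients with many foci can dominate its variance. A power figure that ignores the spread among those patients says little about a comparison of means.

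At stake is the single confirmatory comparison. As written, nobody can say what chance the trial has of showing the effect it assumes.

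**Working it through.** **Inputs.** From {14}: 85% vs 70% lesion-free, 80% power, 5% level, 118 per group. From Trial design {8}: equal allocation, superiority. Three readings are mine: the favourable response means no new SBI, the test is two-sided (sidedness is not stated), and the count distributions below are assumed because the article gives none.

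**Step 1: reproduce the stated figure.** Two proportions, unpooled variance:

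n = (1.960 + 0.842)² × (0.85×0.15 + 0.70×0.30) / 0.15² = 7.849 × 0.3375 / 0.0225 = 117.7, so 118.

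This matches exactly. The pooled-variance version gives 121, and one-sided or continuity-corrected versions (95, 108, 134) do not fit. The figure is a calculation for a binary outcome.

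**Step 2: what the same n means for a difference in means.** With 118 per group, 80% power needs a standardised difference of (1.960 + 0.842) × √(2/118) = 0.365. Suppose patients with lesions have the same count distribution in both arms, with coefficient of variation c. In units of the mean count among patients with lesions, the difference is 0.30 − 0.15 = 0.15 and the average variance is

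[0.30(1 + c²) − 0.09 + 0.15(1 + c²) − 0.0225] / 2.

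| c | standardised difference | approximate power at 118 per group |
|---|---|---|
| 0 | 0.365 | 80% |
| 0.5 | 0.316 | 68% |
| 1 | 0.239 | 45% |
| 1.5 | 0.183 | 29% |

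The stated 80% returns only at c = 0, that is, when all patients with lesions have the same number of foci.

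**Step 3: simulated power.** 118 per arm, lesion-free rates fixed at 70% and 85% throughout, two-sided 5% level.

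| Assumed counts | t-test | Wilcoxon |
|---|---|---|
| Poisson | 84% | 82% |
| Negative binomial, common k = 1 | 88% | 83% |
| Negative binomial, common k = 0.5 | 91% | 85% |
| Negative binomial, common k = 0.25 | 95% | 86% |
| Negative binomial, common k = 0.15 | 98% | 87% |
| Equal counts among patients with lesions: mean 2, k = 1 | 60% | 77% |
| Same, mean 3, k = 1 | 55% | 78% |
| Same, mean 3, k = 0.5 | 46% | 79% |
| Same, mean 4, k = 0.3 | 35% | 79% |

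In the last four rows the count among patients with lesions is 1 plus a negative binomial with dispersion k. The chi-square test on any lesion stays at about 78% to 81% in every row, as it must with fixed rates. Across repeated simulations of such scenarios the Wilcoxon test stayed between 77% and 88%.

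**Step 4: why the rows differ.** With equal counts among patients with lesions, the mean falls by 50% (0.30 to 0.15 patients affected, same burden). Under the common-k negative binomial with k = 0.15, the mean falls from 1.467 to 0.293, or 80%. The same 85% vs 70% assumption is compatible with both.

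**The case against.** **The t-test is not fixed for this endpoint.** Section {20a} is a general rule, it also names ANCOVA, it allows medians in description, and it plans a skewness check. What follows from high skewness may well be in an analysis plan that is not shown, so its absence here is not a fault. That stands. But the mismatch between {12} and {14} does not depend on the t-test: no mean or dispersion supports a power claim for the count under any test.

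**A reader might infer that the trial is underpowered.** The documents do not support this. The low figures require equal counts among patients with lesions in both arms. The Rationale reports that in one transcatheter aortic valve implantation (TAVI) trial more than 10 foci occurred only in controls, which suggests that burden may fall too. If the conditional mean were also 39% lower with the filter (an assumption), t-test power in four equal-shape scenarios rises to 98%, 94%, 85% and 69%. Against that, the percentage reductions the Rationale reports for this device are 39% and 51%, smaller than the overall falls implied by the high-power rows. Neither side settles it: the article itself says that TAVI emboli differ from those of the appendage, and in the trial with more than 10 foci only 13% of controls were lesion-free, against 70% assumed here.

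**Two further inferences fail.** First, count and proportion results do not compete for the verdict, because the count is the only primary endpoint. Second, the sizing event omits stroke foci, but at the 0.17% periprocedural stroke risk given in Background {6a} this is 0.0017 × 120 = 0.2 patients per arm, which is negligible.

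**Conclusion.** The mismatch is certain from the text and confirmed by exact reproduction of 118 as a two-proportion figure. The stated 80% power does not apply to the primary analysis as written.

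Its size depends on assumptions. Holding the plan's 70% and 85% lesion-free rates, t-test power at 118 per group runs from about 30% to 98% over the distributions tried. That range is not a bound: in the formula of step 2, c = 2 gives 20%. The proper conclusion is that power is not established, not that it is low. In several scenarios the t-test does better than the rank test. The case for a rank test is that its power moves little across the scenarios and stays near the planned 80%, not that it always wins.

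**What to change.** Align endpoint, test and power statement before unblinding. N stays at 120 per group. Either option will do.

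- **(a) Keep the count as primary.** In {20a}, name the Wilcoxon rank-sum test for the number of new foci. In {14}, say that 80% is the power for the proportion without new lesions, and give power for the count under a stated count assumption. Report the proportion with at least one new SBI or stroke focus as a supportive analysis. Changing the test alone is not enough, because {14} would still describe a different endpoint.
- **(b) Make the proportion primary.** In the Abstract and {12}, define the primary endpoint as at least one new SBI or stroke focus, tested by chi-square with a risk difference and confidence interval, and move the count to secondary. Section {14} then fits, once its event is worded the same way.

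The cost is a change of wording in the protocol and any analysis plan, with no extra patients or data. The effect is reported as a rank measure or a risk difference instead of a mean difference. Under (a), some count distributions give the rank test somewhat less power than the t-test, for example 87% against 98% with a negative binomial at k = 0.15.

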In summary, while LAAC procedures have demonstrated efficacy in stroke prevention, the potential risks, including SBI and its impact on cognitive and mood disorders, must be thoroughly evaluated. The potential beneficial effect of cerebral protection devices in reducing the risk of SBI and the subsequent cognitive impairment and mood disorders associated with LAAC procedures would have significant implications for clinical management standards. The findings of this study can potentially shape guidelines and recommendations for the use of cerebral protection devices during LAAC and other left atrial interventions, such as AF ablation. If the study demonstrates a favorable outcome with reduced SBI incidence and improved cognitive and mood outcomes in patients receiving cerebral protection devices during LAAC, it suggests that similar benefits could be extrapolated to other left atrial interventions. This would support the use of neuroprotection devices in procedures like AF ablation, where the risk of embolic events and subsequent brain injury may also be present. However, it is important to await the current study’s results to evaluate the impact and benefits of cerebral protection devices on SBI and related outcomes in patients undergoing LAAC.

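### The declared primary endpoint is a number of lesions, but the 118 per arm and 80% power are for the proportion of patients with no new SBI, so the stated power does not belong to the primary endpoint

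*Protocol article*

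**What the plan says.** Outcomes {12} states that the "primary endpoint is the number of new SBIs or stroke foci in the DW MRI". The Methods part of the Abstract says the same: "The primary endpoint of the study is the number of new SBIs or stroke foci". For a comparison between arms, this has to be a count per patient.

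Sample size {14} is built on something else. It assumes a favourable response in 85% of protected patients and, for controls, that "the absence of new SBI on DW MRI in the control group would affect 70% of patients". From these it derives at least 118 per group for 80% power at a 5% significance level. It then allows 2% for withdrawal and enrols 120 per group. It gives no mean count, standard deviation or dispersion. The proportion of patients free of new SBI does not appear among the primary or secondary endpoints in Outcomes {12}.

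Statistical methods {20a} allocates tests by type of variable: t-tests and "ANCOVA for quantitative variables. A chi-square test will be used to compare distributions between the two groups for qualitative variables". It names no test for the primary endpoint specifically.

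The Objectives {7} hypothesise that the device "would mitigate the risk of SBI, cognitive decline, and depression in these patients", and the Discussion looks ahead to a favourable result "with reduced SBI incidence and improved cognitive and mood outcomes".

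**The concern.** The endpoint that is declared and the endpoint that is powered are different variables. Under {20a} they go to different tests: the count to a t-test or ANCOVA, the proportion to a chi-square test. Two things follow.

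First, the 80% in {14} cannot be quoted as the power of the primary analysis. Power for a mean count depends on how many lesions affected patients have and how variable that number is, and the protocol is silent on both.

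Second, the document leaves room for two primary analyses that answer different questions. One asks whether fewer patients are affected, the other whether there are fewer lesions on average. They can give opposite answers in the same trial. A significant difference in mean count would not by itself support a statement that fewer patients had an SBI.

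**Working it through.** **Inputs from the protocol.** Free of new SBI: 70% v 85%, so 30% v 15% affected; 80% power; 5% significance; 118 per arm ({14}); 1:1 allocation (Trial design {8}). Sidedness is not stated; two-sided reproduces the figure.

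**Step 1: reproduce 118.** Two proportions, unpooled variance:

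n = [0.70×0.30 + 0.85×0.15] × (1.960 + 0.842)² / 0.15² = 117.7, rounded up to 118.

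This matches exactly. Power at 118 per arm is 80.1% (unpooled) or 79.2% (pooled). The calculation is sound, and it is binary.

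**Step 2: a t-test on the count, same 30% v 15%.** Assume that affected patients have the same lesion distribution in both arms, with mean m and coefficient of variation CV. Then:

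- difference in means = 0.15m
- control variance = m²[0.30(1 + CV²) − 0.09]
- device variance = m²[0.15(1 + CV²) − 0.0225]

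m cancels, so power depends on CV alone. At CV = 1 the bracketed terms are 0.51 and 0.2775, which sum to 0.7875. The standard error is √(0.7875/118) = 0.0817, and 0.15/0.0817 − 1.96 = −0.12, so power is 45%. The n for 80% power would be 0.7875 × (1.960 + 0.842)² / 0.15² ≈ 275 per arm.

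| CV among affected patients | 0 | 0.5 | 0.7 | 1 | 1.5 | 2 |
|---|---|---|---|---|---|---|
| t-test power, 118 per arm | 80% | 68% | 59% | 45% | 29% | 20% |

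**Step 3: simulation at 118 per arm, two-sided 5%, 6,000 trials per scenario.** All lesion distributions are assumptions.

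| Scenario | t-test | chi-square on any lesion |
|---|---|---|
| 30% v 15% affected; geometric, mean 1.5 / 2 / 3 / 5 per affected patient in both arms | about 65 / 59 / 55 / 51% | about 80% |
| 30% v 15%; Poisson or negative binomial with common dispersion | 84–96% | 79–80% |
| 30% v 15%; geometric, mean 3 v 2 | 91% | 80% |
| 30% v 15%; geometric, mean 3 v 1.5 | 99% | 80% |
| 30% in both arms; geometric, mean 5 v 2 | 85% | 5% |
| 30% v 15%; geometric, mean 2 v 4, so equal overall means | 6% | 80% |

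Independent runs of the first row differ by about one point (up to 66% at mean 1.5).

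A Wilcoxon test has about 78–80% power in the first row. It is not a test of mean burden, however: with 30% affected in both arms and mean lesions 3 v 1.5, it rejects in about 10% of trials, against 67% for the t-test and 5% for chi-square.

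**The case against.** The best reply is that {20a} is a generic paragraph. It names no primary test, mentions a skewness index and allows medians, so skew is expected. The choice of test for a skewed count could properly sit in an analysis plan that is not shown. This much stands: the t-test figures follow from a literal reading of {20a} and do not describe a fixed primary test. With log(1 + count) the t-test has about 68–75% power when only incidence changes, and a rank test about 78–80%.

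It does not remove the point. An analysis plan could name a test, but {12} and {14} would still disagree about what is primary.

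Four stronger readings are tempting, and the documents do not support them.

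- *The trial is underpowered.* Power for the count may be below or above 80%. The Rationale cites a TAVI trial of this device reporting reductions in both number and volume of lesions, so the scenarios above 80% are plausible too.
- *The scenarios bound the true power.* They do not. Every lesion distribution is assumed, and more extreme ones move the figure further.
- *The type I error is inflated.* If either test could be reported as primary, simulation under no effect gives about 7–8%. That presumes picking the favourable result, which the plan does not propose.
- *Stroke foci are materially miscounted.* {14} mentions only SBI, while the endpoint includes stroke foci. The Background gives periprocedural stroke risk as 0.17%, and 0.0017 × 240 ≈ 0.4 patients. This is a wording point.

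The phrases on risk and incidence in the Objectives and Discussion lean towards the proportion but do not exclude a count.

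**Conclusion.** The mismatch is real and should be corrected. The 118 per arm is right for 70% v 85% of patients without new SBI. That endpoint is not declared, and the 80% power does not carry over to the declared count. Power for the count cannot be derived from the protocol.

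The size is illustrative only and rests on the assumed distributions. With geometric counts and a device effect on incidence alone, a t-test has roughly 50–66% power, and less with heavier tails (20% at CV 2). If lesions per affected patient also fall clearly, it has about 90% or more. The firmest consequence is that the two analyses can disagree: 85% v 5% rejection when incidence is equal and mean lesions are 5 v 2.

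**What to change.** Amend the protocol before any unblinded look, so that the Abstract, {12}, {14} and {20a} name one primary endpoint and one test.

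**(a) Keep the declared count.** In {20a}, name a test suited to a skewed, zero-heavy count (Wilcoxon or negative binomial) in place of the t-test. Choose between them deliberately, since the rank test responds mainly to incidence. In {14}, describe the 80% as power for the proportion without new foci, and give power for the count under a stated mean and dispersion. Correcting this power statement is the minimum change. Cost: wording and a short calculation; the declared endpoint is untouched.

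**(b) Make the proportion primary.** Define it as patients with at least one new focus, silent or stroke, tested by chi-square and reported as a risk difference with a 95% CI. The 118 per arm and 80% then stand. Make the count the first secondary endpoint. Cost: a protocol and registry amendment that changes a declared primary endpoint after recruitment began (26 May 2023, Trial status), and a primary result that ignores lesion number.

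Under either option, align the SBI-only wording in {14} with the endpoint's SBI or stroke foci. Neither option needs extra scans or readings. (b) needs no extra patients; under (a), whether 240 is enough depends on the assumptions then stated.
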